# Robot-assisted laparoscopic radical cystectomy with intracorporeal ileal conduit diversion versus open radical cystectomy with ileal conduit for bladder cancer in an ERAS setup (BORARC): protocol for a single-centre, double-blinded, randomised feasibility study

**DOI:** 10.1186/s40814-022-01229-3

**Published:** 2023-01-13

**Keywords:** Randomised controlled trial, Blinding, Radical cystectomy, Bladder cancer, Urothelial carcinoma, Robotic surgery, Open surgery

## Abstract

**Background:**

Radical cystectomy (RC) with urinary diversion is the recommended treatment for selected cases of non-metastatic high-risk non-muscle-invasive and muscle-invasive bladder cancer. It remains unknown whether robot-assisted laparoscopic cystectomy (RARC) offers any advantage in terms of safety compared to open cystectomy (ORC) in an Enhanced Recovery After Surgery (ERAS) setup. Blinded randomised controlled trials (RCTs) between RARC versus ORC have never been conducted in cystectomy patients. We will investigate the feasibility of conducting a double-blinded RCT comparing ORC with RARC with intra-corporal ileal conduit (iRARC) in an ERAS setup.

**Methods:**

This is a single-centre, double-blinded, randomised (1:1) clinical feasibility study for patients with non-metastatic high-risk non-muscle-invasive or muscle-invasive bladder cancer scheduled for cystectomy. All participants are recruited from Rigshospitalet, Denmark. The planned sample size is 50 participants to investigate whether blinding of the surgical technique is feasible. Participants and postoperative caring physicians and nurses are blinded using a pre-study designed abdominal dressing and blinding of the patient’s electronic health record. Study endpoints are assessed 90 days postoperatively. The primary aim is to study the frequency and pattern of unplanned unblinding after surgery and the number of participants who cannot guess the surgical technique at the day of discharge. Eleven secondary endpoints are assessed: length of stay, days alive and out of hospital, in-hospital complication rate, 30-day complication rate, 90-day complication rate, readmission rate, quality of life, blood loss, pain, rate of moderate/severe post-anaesthesia care unit (PACU) complications, and delirium. Participants are managed in an ERAS setup in both arms of the trial.

**Discussion:**

We report on the design and objectives of a novel experimental feasibility study investigating whether blinding of the surgical technique in cystectomy patients is possible. This information is essential for the design of future blinded trials comparing ORC to RARC. There is a continued need to compare RARC and ORC in terms of both efficacy, safety, and oncological outcomes. Estimated end of study is March 2021.

**Trial registration:**

ClinicalTrials.gov ID: NCT03977831. Registered on the 6th of June 2019.

**Supplementary Information:**

The online version contains supplementary material available at 10.1186/s40814-022-01229-3.

## Introduction

### Background and rationale

Radical cystectomy (RC) with urinary diversion for bladder cancer (BC) is the recommended treatment in selected cases of high-risk non-muscle-invasive BC and muscle-invasive BC [1]. The procedure is associated with a high risk of complications and often long recovery. There has been an increasing interest in introducing minimally invasive surgery in cystectomy patients to reduce complications and enhance recovery associated with RC. The introduction of robot-assisted laparoscopic RC (RARC) has led to several studies comparing RARC to standard open radical cystectomy (ORC) [2]. To date, there is no evidence that RARC reduces complications associated with RC compared to ORC [3].

Secondly, Enhanced Recovery After Surgery (ERAS) protocols have been promoted to reduce both complications and length of stay (LOS) associated with RC. ERAS protocols focus on improving and standardising perioperative care with an emphasis on evidence-based principles. ERAS protocols in RC have shown a decrease in complication rate and LOS without increasing the readmission rate, but it remains unknown if recovery is faster with RARC compared to ORC [4]. Currently, no RCTs, including blinding, comparing ORC and RARC in a contemporary perioperative ERAS setup have been published [5–9].

Blinding seeks to prevent ascertainment bias as care providers’ expectations may affect subjective outcomes [10]. Blinded RCTs in surgery are rare and has never previously to our knowledge been conducted for RC. We believe it is possible to conduct a blinded RCT in RC as blinded RCTs comparing open and laparoscopic procedures in abdominal surgery have been shown feasible [11–14].

This protocol describes an ongoing RCT assessing the feasibility of a double-blinded setup comparing ORC and robot-assisted laparoscopic RC with intracorporeal urinary diversion (iRARC) in an ERAS setup. The aim of the study was to test if blinding of the surgical technique is possible and secondly to describe efficacy and safety outcomes for the two surgical methods in an ERAS protocol.

## Methods/design

This study is designed as a randomised, controlled, patient, and care provider blinded single-centre feasibility study with 1:1 ratio allocation of participants to either ORC or iRARC. We will enrol a total of 50 participants. The clinical assumption is that the planned sample size is sufficient to explore the primary outcome and describe if blinding is feasible [15].

This trial is registered on the 6th of June 2019 at ClinicalTrials.gov ID: NCT03977831 (https://clinicaltrials.gov/ct2/show/NCT03977831?term=NCT03977831&draw=2&rank=1). The protocol version is the original from the 14th of December 2018: Protocol-60292_v1_141218. The protocol for this randomised trial is reported in compliance with the Standard Protocol Items Recommendations for Interventional Trials (SPIRIT) guidelines (see appendix for SPIRIT checklist) [16].

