### Assignment of interventions

Participants will be randomly assigned to either ORC or iRARC with a 1:1 allocation using the randomisation module of Research Electronical Data capture (REDCap) [17, 18]. The allocation sequence is a computer-generated list of random numbers transferred to REDCap. No stratification will be applied. Block randomisation will be used to ensure equal distribution between the two arms at any time during the trial. The block sizes will not be disclosed to ensure concealment. The web-based randomisation system ensures concealment. A collaborator with no clinical involvement has transferred the randomisation code to REDCap. Allocation concealment will be ensured as no other person has access to the randomisation code. After storing in REDCap, changing the randomisation sequence is impossible. The randomisation is performed by the Head Nurse at the Department of Urology or substitute who is the only person with access to the randomisation module in REDCap. The randomisation will be performed the day before surgery. Upon randomisation, only the staff in the operating room and the surgeons are informed. The participants, treating physicians, nurses at the PACU, and the urological ward as well as the outcome assessor are all blinded until discharge. Participants are only blinded until discharge as blinding after discharge is impossible.

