### Outcomes

#### Primary outcome

The success of blinding will be determined by (1) the number and proportion of participants with unplanned unblinding before discharge in the two treatment arms and (2) the number of participants, attending doctors, and nurses guessing the correct method of operation at unblinding beyond the level of chance. A previous study from our institution has found a reoperation rate of 22% during the first 90 days after RC with the majority being reoperated during their index hospitalisation [20]. As a reoperation necessitates unblinding, a proportion of < 25% of participants with unplanned unblinding is considered succesfull.

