### Statistics

For the primary outcome, the proportion of participants with unplanned unblinding before discharge in the two treatment arms will be calculated using descriptive statictics. The number of participants guessing the correct method of operation at unblinding beyond the level of chance is calculated using Bang’s Blinding Index [25].

Analyses and data summaries will be conducted using the groups to which the patients were randomised, and patients will be included regardless of whether they received the allocated treatment, or they were unblinded during admission (“intention to treat”). Baseline characteristics of the included patients will be summarised by trial arm using descriptive statistics with continuous variables reported as the median and interquartile range (IQR) and categorical values in numbers and percentages of the total group. Full details will be described in the statistical analysis plan for the study.

We expect the amount of missing data to be low as most data is extracted from the EHR. We also expect dropouts to be low given the non-experimental design of the study with no extra planned physical visits out of the ordinary follow-up. In the case of dropouts, we expect these to be “missing not at random.” Therefore, multiple imputation will be used for handling missing data.

The protocol, template for the eCRF including the data collection instruments, de-identified data, and the statistical code are not made publicly available but will be delivered upon reasonable request by contacting the PI or the corresponding author. However, access to de-identified data will require an application to and approval from the Danish Data Protection Agency.

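### With about 25 answers per arm, a Bang's index that does not exceed chance is weak evidence that the blind held, yet exceeding chance is the only criterion for guessing

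*Protocol article*

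**What the plan says.** Under Methods/design the protocol article fixes the size ("We will enrol a total of 50 participants") and describes a "single-centre feasibility study with 1:1 ratio allocation of participants to either ORC or iRARC". Under Assignment of interventions, blocking is meant to keep the arms equal, so full accrual gives 25 per arm. The size is justified in one sentence with one citation, as a clinical assumption that the "planned sample size is sufficient to explore the primary outcome and describe if blinding is feasible". No expected precision is given.

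The Primary outcome section makes blinding success depend on two components. Unplanned unblinding before discharge has a numeric limit, below 25%. The other component is the number of participants, doctors and "nurses guessing the correct method of operation at unblinding beyond the level of chance", with no numeric limit. The Statistics section names the method for participants: the number "guessing the correct method of operation at unblinding beyond the level of chance is calculated using Bang"'s index. Interventions and blinding offers each respondent three answers: open, robot-assisted, or do not know.

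**The concern.** The guessing component has one dividing line, chance, and no margin. Under such a criterion the outcome that counts in favour of blinding is a failure to find something, and a small sample makes that failure more likely. The fewer answers there are, the easier it is for a leaking blind to look intact.

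The article presents the result as essential for designing later blinded trials of the two operations. If an index compatible with chance were carried forward as a working blind, those trials could rely on a dressing and masking procedure that let a substantial share of patients or staff identify the operation.

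**Working it through.** **Inputs from the protocol article.** 50 participants, 1:1 with blocking, so n = 50/2 = 25 per arm. Three answer categories. The index is Bang's, which is defined within an arm.

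**Assumptions, because the article gives none.** 95% two-sided limits; a do-not-know share (DK) of 0%, 30% or 50%; one answer per patient from each respondent group.

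**No figure to reproduce.** The article gives no precision, power or target index for 50, so the check is what 25 answers deliver.

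**Step 1: precision at an index of 0.** With BI = p(correct) − p(wrong), Var(BI) = [p(correct) + p(wrong) − BI²]/n. At BI = 0 this is (1 − DK)/25.

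- DK 0%: SE = √(1/25) = 0.200; half-width 1.96 × 0.200 = 0.39.
- DK 30%: SE = √(0.70/25) = 0.167; half-width 0.33.
- DK 50%: SE = √(0.50/25) = 0.141; half-width 0.28.

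**Step 2: the upper limit as a share of correct guesses.** Among those who guess, the share is 0.5 + BI/[2(1 − DK)]. Among all respondents it is (1 − DK + BI)/2.

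- DK 0%: 0.5 + 0.392/2 = 69.6% on either basis.
- DK 30%: 0.5 + 0.328/1.4 = 73% of guessers; (0.70 + 0.328)/2 = 51% of all.
- DK 50%: 0.5 + 0.277/1.0 = 78% of guessers; (0.50 + 0.277)/2 = 39% of all.

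**Step 3: what counts as not beyond chance (DK 0%).** With 17 of 25 correct (68%), BI = 0.36, the Wald interval is −0.006 to 0.73 and the exact two-sided p is 0.108. With 18 of 25 (72%), p = 0.043. So 68% observed correct answers would still not exceed chance.

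**Step 4: how often a real leak is missed.** Take a true index of 0.30 and sum the multinomial probabilities of all outcomes of 25 answers whose two-sided 95% Wald interval does not lie above 0.

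- DK 0% (65% correct, 35% wrong): missed in 69% of trials.
- DK 30% (50% correct, 20% wrong): missed in 51%.
- DK 50% (40% correct, 10% wrong): missed in 35%.

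A one-sided 95% rule gives about 53%, 39% and 25%. With DK 0%, a true 70% correct (index 0.40) is flagged in 51% of trials under the two-sided rule and 68% under the one-sided rule.

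**Step 5: scale.** With DK 0%, a half-width of 0.30 needs (1.96/0.30)² = 42.7, so about 43 answers per arm. A half-width of 0.20 needs (1.96/0.20)² = 96, so about 96 to 97.

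**The case against.** The strongest reply is that the article claims little. The sufficiency sentence is openly labelled a clinical assumption, speaks of exploring and describing, and belongs to a feasibility study. No calculation is misstated. The Statistics section says only that the index is calculated, specifies no test, and leaves full details to an analysis plan that is not shown and may well contain intervals. All of that stands. It does not reach the criterion itself, because the Primary outcome section says success is determined by guessing beyond chance and gives that component no other limit.

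A second reply is that the do-not-know option changes the figures. This also stands. The 69% miss rate applies only if nobody uses that option. Large leaks are usually caught: if 70% of all respondents are correct and 10% or 20% do not know (index 0.50 or 0.60), the two-sided rule flags it in 83% or 98% of trials.

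Stronger readings are tempting, and the article does not support them:

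- *Blinding is the trial's only purpose.* The Background also names describing efficacy and safety as a second aim.
- *Any interval that includes 0 is inconclusive.* An intact blind gives such an interval about 95% of the time at any sample size, and a narrow interval around 0 is the best evidence there is.
- *Staff answers are clustered, so precision is worse still.* Repeat raters on one ward are plausible, but the article documents neither their number nor their overlap.
- *The data could never exclude that most respondents knew.* At an observed index of 0 the upper limit is 51% of all respondents with DK 30%, and 39% with DK 50%.

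**Conclusion.** The point holds as a weakness in the conclusion rule and in the unsupported sufficiency assumption; it is not an arithmetic error. At 25 answers per arm and respondent group, an index at chance leaves values up to about 0.28 to 0.39 unexcluded, and a true index of 0.30 is missed in roughly one third to two thirds of trials, depending on how many respondents do not know.

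This rests on two-sided 95% limits, the assumed do-not-know shares, analysis by arm and full accrual. If only 19 per arm answered, the half-width with DK 0% would rise to 0.45. Pooling both arms would reduce it to 0.28, but the article does not mention pooling. The change should be made: it bears directly on a component of the primary outcome and needs wording only.

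**What to change.** 1. **Methods/design:** replace the sufficiency assumption with the expected precision, a 95% half-width for the per-arm index at 0 of about 0.39, 0.33 or 0.28 for do-not-know shares of 0%, 30% or 50%.
2. **Primary outcome and Statistics:** state that failure to exceed chance does not by itself count as success. Report the index per arm and respondent group with its 95% interval and the largest index not excluded, also expressed as a share of correct guesses with its denominator (all respondents or those who guessed).
3. **Conclusion rule:** name a tolerable index before unblinded analysis. Conclude that blinding held on this component only if the upper limit lies below it. If not, and the lower limit does not exceed chance, call the component inconclusive.

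The cost is wording in the protocol and analysis plan. No patients or data are added, which suits a trial reporting 47 enrolled. The drawback is a less favourable claim: with no do-not-know answers, even an observed index of 0 cannot meet a tolerable index below about 0.39, so a strict limit will often end as inconclusive. That reflects what 25 answers per arm can show.

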### Objectives

#### Primary objective

The primary objective of this study is to analyse the number of patients with unplanned unblinding before discharge and the number of patients who cannot infer the type of surgery.

#### Secondary objectives

The secondary objective of this study is to compare LOS, days-alive-and-out-of-hospital (DAOH), in-hospital complication rate, 30-day complication rate, 90-day complication rate, readmission rate, quality of life (European Organisation for Research and Treatment of Cancer (EORTC) Quality of Life Questionnaire QLQ-C30 and QLQ-BLM30), blood loss (estimated and hidden), pain, rate of moderate/severe post-anaesthesia care unit (PACU) complications (Danish Society of Anaesthesiology and Intensive Care (DASAIM) discharge criteria), and delirium in ORC versus iRARC.

### Study setting

All participants are recruited from and operated at Copenhagen University Hospital, Rigshospitalet. The Department of Urology, Rigshospitalet, is one of two tertiary referral centres for cystectomy in eastern Denmark.

Two highly experienced surgeons are assigned to perform iRARC and ORC (complete procedure), respectively. The surgeon who performs ORC has an experience of >500 ORCs. The surgeon who performs iRARC has performed >100 iRARCs. All procedures will be performed with one of three urology speciality registrars as assistants who are all experienced with both iRARC and ORC.

### Eligibility criteria and inclusion

#### Inclusion criteria

High-risk non-muscle-invasive including treatment-resistant carcinoma in situ or muscle-invasive urothelial carcinoma of the bladderAge > 18 yearsPatient preference for an ileal conduit as urinary diversionInformed consent

#### Exclusion criteria

Inability to speak/understand DanishInability to cooperate for inclusion in the studyNeed for concomitant extended surgery (i.e., nephroureterectomy)Prior downstaging chemotherapy (neoadjuvant chemotherapy is allowed)Metastatic diseasePrior pelvic radiation therapyPrior major extensive abdominal or pelvic surgeryPrior peritonitisConditions contraindicating Trendelenburg’s position.

Patients potentially eligible for the study are screened at the time of electronic referral. All bladder cancer patients are seen in the out-patient clinic every Thursday and one Friday per month. Pre-planned surgical slots for protocol patients are planned one month in advance. Eligibility is assessed in the outpatient clinic at the preoperative consultation. Patients will receive comprehensive oral information as well as written information material. Patients will be informed that their agreement to participate is voluntary. Hereafter, a second consultation is scheduled at which potential participants will have the opportunity to ask questions and have an informed discussion. Upon oral consent to participate, written consent from patients will be obtained by [name] or [name].

### Assignment of interventions

Participants will be randomly assigned to either ORC or iRARC with a 1:1 allocation using the randomisation module of Research Electronical Data capture (REDCap) [17, 18]. The allocation sequence is a computer-generated list of random numbers transferred to REDCap. No stratification will be applied. Block randomisation will be used to ensure equal distribution between the two arms at any time during the trial. The block sizes will not be disclosed to ensure concealment. The web-based randomisation system ensures concealment. A collaborator with no clinical involvement has transferred the randomisation code to REDCap. Allocation concealment will be ensured as no other person has access to the randomisation code. After storing in REDCap, changing the randomisation sequence is impossible. The randomisation is performed by the Head Nurse at the Department of Urology or substitute who is the only person with access to the randomisation module in REDCap. The randomisation will be performed the day before surgery. Upon randomisation, only the staff in the operating room and the surgeons are informed. The participants, treating physicians, nurses at the PACU, and the urological ward as well as the outcome assessor are all blinded until discharge. Participants are only blinded until discharge as blinding after discharge is impossible.

### Interventions and blinding

Participants will be randomised 1:1 to receive either ORC or iRARC. All participants are treated in an ERAS setup (Table 1). Upon randomisation, only the operating surgeons, the assistant surgeon, the operating room, and anaesthesiological staff will be informed of the assigned allocation, and none of them are involved in the postoperative care. The treatment allocation is concealed from the patients, treating physicians, staff at the PACU and the urological ward, and the outcome assessor until discharge.

**Table 1 Tab1:** List of components in Rigshospitalet’s Enhanced Recovery After Surgery protocol for radical cystectomy

Preoperatively	
- Pre-operative education and counselling: surgical details, hospital stay, and discharge criteria	
- Stoma education with a specialised stoma nurse	
- Preoperative medical evaluation and optimization	
- Advice and support for smoking cessation and reduction of alcohol intake	
- Instruction on postoperative mobilisation and physiotherapy	
- Anesthesiologic assessment	
Day before operation	
- Admission to hospital	
- Normal diet with no restrictions	
- Rectal enema the night before surgery; omission of mechanical bowel preparation	
- Pharmacological thrombosis prophylaxis with LMWH (Tinzaparin 4500 IE)	
POD 0: preoperatively	
- Preoperative fasting: normal diet until 6 h and clear fluids until 2 h before anaesthesia	
- Preoperative pain medication: Gabapentin 600 mg + Paracetamol 1 g.	
- No long-acting sedatives	
- Elastic compression stockings for thrombosis prophylaxis	
POD 0: intraoperatively	
- Antimicrobial prophylaxis: i.v. Cefuroxime 3 g intraoperative and skin preparation	
- Anaesthesia is similar between groups, including orotracheal intubation, total intravenous anaesthesia (Cisatracurium, Remifentanil, and Propofol), Ondansetron 4mg, Dexamethasone 24 mg, Tranexamic acid 1000mg, i.v. oxycodone and regional anaesthesia using rectus sheath blocks (2 mg bupivacaine/kg body weight) at the end of surgery without epidural	
- Central venous catheter (vena jugularis interna dexter)	
- Radial arterial line	
- Prevention of intraoperative hypothermia (Bair Hugger)	
- Nasogastric tube inserted and removed before extubating	
- No resection site drainage	
- Bilateral ureteric stents	
POD 0: postoperatively	
- Admission to the postoperative care unit until POD1	
- Chewing gum (throughout admission to hospital)	
- Antibiotics Cefuroxime 1500 mg x 3 i.v. (continued for 3 days)	
- Thrombosis prophylaxis: LMWH (continuing 4 weeks postoperatively) and compression stockings (until discharge)	
- Analgesics: Gabapentin 600mg+300 mg (continued for 3 days) + Paracetamol 1 g x 4 (continued throughout admission), *short-acting* opioids (oxycodone or morphine) if necessary	
- Laxatives: macrogol 1 sachet x 2	
- Antiemetics: Metoclopramide 10 mg if needed	
- Mobilisation: sitting and standing in the evening	
- Oral nutrition: maximum 1 L I fluid, no solids	
- Fluid strategy: Goal directed fluid therapy by stroke volume optimization	
- Continuous Positive Airway Pressure (CPAP) every second hour except during nighttime (24–06)	
POD 1	
- Admission to the urological ward	
- Medication and thrombosis prophylaxis: see “POD 0 postoperatively”	
- Oral nutrition: solids as tolerated, maximum of 1 L of fluids	
- Mobilisation: sitting as much as possible in a chair, walk minimum 2 x 60 m with a walking frame with wheels	
- Self-administration of thromboprophylaxis injections and individually adapted level of self-sufficient care for ileal conduit throughout their hospital stay in preparation for discharge	
POD 2	
- Medication and thrombosis prophylaxis: see “POD 0 postoperatively”	
- Oral nutrition: no restrictions	
- Mobilisation: out of bed minimum 2 x 3 h, walk minimum 3 x 60 m	
POD 3	
- Medication: see “POD 0 postoperatively”	
- Oral nutrition: no restrictions	
- Mobilisation: out of bed minimum 8 h, walk minimum 3 x 60 m	
- Discharge if fulfilling discharge criteria	
POD 4 and until discharge	
- Medication: Paracetamol 1 g x 4, macrogol 1 sachet x 2. Metoclopramide and short-lasting opioids if needed.	
- Mobilisation: as POD 3	
Discharge criteria	
- Adequate pain control	
- Independently mobilised	
- Instructed in stoma care, and establishment of post-discharge specialised assistance if needed - No sign of ileus	
- Adequate oral intake	
Discharge	
- Unblinding	
- Provision of support network including district nurse and urology nurse	
- Information on signs and symptoms of complications. Informed to contact the department by telephone at all hours in case of signs of complications for consultation with a urological nurse or doctor on further actions.	
Post discharge	
- Removal of ureteric stents and skin suture on POD 10 with creatinine blood sample on POD 11	
- Contact with a nurse by telephone the first Thursday after discharge	
- Follow-up after discharge will adhere to local and national guidelines with planned outpatient visit (1) 3 weeks postoperatively for the result of pathology report and planning of oncologic follow-up, and (2) 8 weeks postoperatively for a 99m Technetium-mercaptoacetyltriglycine renography control.	

*POD* postoperative day, *LMWH* low molecular weight heparin

Before the start of the protocol, all study personnel have been trained in the protocol setup. The procedure will be booked as an open procedure in the electronic operating booking system and scheduled from 9 a.m. to 2 p.m. regardless of the method of surgery used. At admission, a note stating that the patient is included in this project will be placed on the patient’s bed. All personnel, including porters, are instructed not to discuss the method of the surgical procedure with the patient. All patients are operated in the same operating theatre in which the da Vinci® Surgical System robot is placed. Anaesthesia is similar between groups, including orotracheal intubation, total intravenous anaesthesia (cisatracurium, remifentanil, and propofol), i.v., oxycodone and regional anaesthesia using rectus sheath blocks (2 mg bupivacaine/kg body weight) at the end of surgery without an epidural. No pre-planning of the operating theatre is performed before the patients are sedated. Both ORC and iRARC follow the same surgical template which includes pelvic lymph node dissection and urinary diversion with an ileal conduit. The extent of the lymphadenectomy will be with the following boundaries: cranially the aortic bifurcation, laterally the genitofemoral nerves, anteriorly the pubic symphysis and the inguinal ligaments, inferiorly the pelvic floor, and posteriorly including the pre-sacral lymph nodes. All wounds are closed using non-absorbable suture. Both primary surgeons and the assisting surgeon will stay in the operating room or an adjacent room to the operating theatre throughout the entire pre-booked time period. The window in the door to the operating room will be covered by a curtain. The operating room is not located adjacent to the other urological operating rooms and no surgeon from the urological ward will pass the used operating room. A temporary standard operation report is used for all patients. In this description, important information on pathology findings and intraoperative complications are included in a manner that does not reveal the surgical method, but data on estimated blood loss (EBL) and time of surgery are left out. A detailed and final operation report will be written by the primary surgeon and kept electronically at the primary surgeon’s password-protected personal drive. The final operation report will be placed in the electronic health record (EHR) at discharge. A printed version of the temporary standard operation report will be kept in a sealed envelope in a hidden place at the Department of Urology. If necessary, this can be obtained at any time by contact with the principal investigator (PI). The abdomen will be dressed to cover wounds from both an ORC and an iRARC (Fig. 1). An adhesive non-transparent, highly absorbent dressing (i.e., Allevyn®) will be used to cover possible exuding from the wounds. The dressing is applied by the surgical team in the operating theatre. Patients are admitted to the PACU after the surgery, where similar postoperative care is performed for both groups, including goal-directed fluid therapy by cardiac output monitoring. On POD1 they are transferred to the urological ward unless the DASAIM discharge criteria are not fulfilled [19]. The dressing will not be changed unless required (because of strike-through or lack of adherence). In this case, a nurse from the neighbouring urological ward, who is not otherwise involved in the care, will be summoned. When changing the dressing, a pillow will be placed on the chest of the patient to maintain blinding of the patient. In the nurses’ office at the ward, a laminated short guide on what to do in specific situations is placed on the wall. Also, alongside this is placed a template of an abdomen with instructions on how to change and place the dressings to keep it standardised. If at any time it is assessed necessary to inspect the wound (e.g., suspicion of wound dehiscence), this can be done and documented. The dressing will be inspected for strike-through of excess exudate by a person not otherwise involved in the care of the patient at least once a day before rounds and changed if needed. [name] will ensure that participants follow the ERAS protocol. Reasons for not complying with the protocol will be registered. Patients are planned to be discharged on POD3 if fulfilling discharge criteria as outlined in Table 1.
